### Study dropouts and missing data

Subjects can leave the study at any time for any reason if they wish to do so without any consequences. The investigator can decide to withdraw a subject from the study for urgent medical reasons.

Subject will be classified as drop outs for the analyses of the endpoint “quality of ventilation” and “ICU team staff workload” if they did not receive postoperative ventilation for at least 2 h. This also means that if a patient is extubated in the operating room, that patient is considered a dropout. At no time a patient will remain intubated to reach at least 2 h of postoperative ventilation, i.e., extubation is never delayed for study purposes. A dropout rate of 5% has been accounted for in the sample size.

In case of withdrawal after randomization, the subject will not be replaced. Captured data until the moment of withdrawal will be stored and used for analysis. If the subject has not been randomized yet, the subject will be replaced to reach the intended sample size of patients.

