### Statistical analysis

A full statistical analysis plan will be published online before the end of recruitment. All statistical analyses will be conducted according to the modified intention-to-treat principle considering all patients in the treatment groups to which they were randomly assigned, excluding cases lost to follow-up due to withdrawal of consent or cancelation of surgery. For both arms, the baseline characteristics will be expressed as counts and percentages, means and standard deviations, or medians and interquartile ranges, depending on normality of data distribution.

Data analysis will be performed blinded for the allocated study intervention. In all analyses, statistical uncertainties will be quantified with two-sided 95% confidence intervals. A two-sided *p*-value < 0.05 will be considered statistically significant. We will not adjust the *p*-value for multiple comparisons.

For the noninferioirty assessment of duration of ventilation, a one-sided noninferiority hypothesis test with a significance level of 0.025 and presented with a one-sided 97.5% confidence interval will be used. If noninferiority is confirmed, superiority will be tested considering a two-sided 95% confidence interval. Since the proposed approach will use a hierarchical closed-testing procedure examining a single confidence interval, no adjustment of the overall type I error will be done.

Statistical analysis will be performed using the free software program “R” (R Core Team, 2020, Vienna, Austria).

The effects of the intervention on quality of ventilation are analyzed and reported as done in previous studies of automated ventilation, i.e., the *time* spent in predefined zones of ventilation [17, 18]. As an add to the primary endpoint, next to *time* spent in predefined zones, we will also calculate *numbers* of breath in predefined zones. For details, see Appendix 1.

The impact of the intervention on ICU team staff workload is reported as in previous studies collecting data on alarms [12–14, 19].

All other endpoints, including duration of ventilation and ICU and hospital length of stay are reported as numbers and proportions.

Patient flows will be presented in a consolidated standard of reporting trials (CONSORT) flowchart.

Patients’ baseline characteristics will be presented per study arm. The proportion of patients who were treated according to their treatment assignment will be reported by treatment group.

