Comparisons of the collected variables will be performed using *χ*^2^ tests for equal proportion, Student’s *t*-test for normally distributed data and Wilcoxon rank sum tests otherwise.

The database will be locked as soon as all data are entered and all discrepant or missing data are resolved—or if all efforts are employed and we consider that the remaining issues cannot be fixed. At this step, the data will be reviewed before database locking. After that, the study database will be locked and exported for statistical analysis. At this stage, permission for access to the database will be removed for all investigators, and the database will be archived.

No or minimally losses to follow-up for the primary and secondary outcomes are anticipated. Complete case analysis will be carried out for all the outcomes, that is, excluding patients with missing data in the outcome of interest. However, if any missing data is found for the primary outcome, a sensitivity analysis using multiple imputations and estimating equation methods will be performed.

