In critically ill patients, even when ventilation last only some hours, it is recommended to use an appropriate low *V*_T_, to titrate PEEP and inspired fraction of oxygen by means of a PEEP/FiO_2_ table, to target a lower driving pressure, and to avoid both hyperoxia and hyperoxemia. This can be challenging and is time-consuming, especially when ICU teams are less experienced in invasive ventilation. Automated modes have the potential to reduce the time teams spent at the ventilator and the amount of alarms related to ventilation teams have to respond to––however, these modes may also be more difficult to set and “supervise”. One single-center randomized clinical study in Belgium [14] and single-center observational study in France showed that INTELLiVENT-ASV requires fewer manual interventions at the ventilator [13]. One recent single-center observational study in severely ill and difficult to ventilate COVID–19 patients in Switzerland showed that the number of manual interventions at the ventilator was half of that with conventional ventilation [12]. The second hypothesis tested, therefore, is that automated ventilation by means of INTELLiVENT-ASV reduces ICU team staff workload. For this, we capture data using a number of alarms and manual ventilator settings approach.

We will also compare clinically relevant clinical outcomes, duration of ventilation, and lengths of stay in the ICU. These endpoints are chosen for the following reasons: duration of ventilation can be seen as one important patient-centered endpoint: discomfort for patients is reduced with a shorter duration of ventilation—length of stay is an important ICU-centered endpoint, as an increase in ICU stay may translate in a lower number of ICU beds available for care for other patients, and higher costs. Of note, we do not expect a difference in duration of ventilation and lengths of stay in the ICU between the groups.

Ventilation in both groups is highly standardized, in the intraoperative phase during anesthesia and in the ICU when the patient is weaned from invasive ventilation. Other parts of care follow strict local clinical guidelines. POSITiVE II aims at minimizing bias by using concealed allocation and an intention-to-treat analysis with a pragmatic protocol that can be strictly adhered to. POSITiVE II is performed in several European countries, in different types of hospitals, making the results generalizable.

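### Consent withdrawal after randomisation is given two rules: one section uses the data captured so far, another, read plainly, removes the patient from every analysis

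*Protocol article*

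**What the plan says.** Study dropouts and missing data allows two routes out of the trial. The patient may go: "Subjects can leave the study at any time for any reason if they wish to do so without any consequences". The investigator may also act: "The investigator can decide to withdraw a subject from the study for urgent medical reasons". For either route the section then states "In case of withdrawal after randomization, the subject will not be replaced", followed by "Captured data until the moment of withdrawal will be stored and used for analysis".

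Statistical analysis sets the population: "All statistical analyses will be conducted according to the modified intention-to-treat principle". Patients stay in the arm to which they were randomised, but the set is formed "excluding cases lost to follow-up due to withdrawal of consent or cancelation of surgery". Later in the same section there is a separate rule for missing outcomes: "Complete case analysis will be carried out for all the outcomes, that is, excluding patients with missing data in the outcome of interest".

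The Discussion describes the trial as "using concealed allocation and an intention-to-treat analysis", without the word modified. No section says which rule takes precedence for a patient who withdraws consent.

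**The concern.** Consent withdrawal falls under both rules. One keeps what was recorded; the other, read plainly, takes the patient out of all analyses. Whoever builds the analysis set has to choose.

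The choice matters because the key outcomes are complete early. Study endpoints confines the primary outcome to the first 2 h of postoperative ventilation, and duration of ventilation is known at extubation. Follow-up runs on to hospital discharge, so a patient can withdraw consent with one or both outcomes already in the database.

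Minimization of bias places randomisation shortly before surgery and says that those giving care cannot be blinded. Any such exclusion is therefore post-randomisation, and withdrawal could be related to arm. Blinding the analyst does not remove selection that arises from who withdraws. The rule also governs duration of ventilation, which is tested for non-inferiority against a margin of ¾ h.

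**Working it through.** **Comparing the rules by type and timing of exit**

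| Situation after randomisation | Outcomes already captured | Study dropouts rule | Statistical analysis rule, plain reading |
|---|---|---|---|
| Consent withdrawn before ICU ventilation | none for ventilation | nothing to use | excluded; same result for the ventilation outcomes |
| Consent withdrawn after 2 h, before extubation | primary outcome | used | discarded |
| Consent withdrawn after extubation | primary outcome and duration | used | both discarded |
| Withdrawn by the investigator for medical reasons | whatever was recorded | used | not named, so no conflict |
| Surgery cancelled | none for ventilation | does not arise | excluded; no ventilation outcome lost |

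The conflict lies in the second and third rows only.

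**Background: the sample size on which the power figures rest**

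Inputs from Sample size calculation: margin 0.75 h, SD 5.0 h, true difference −1.01 h, one-sided alpha 0.025, power 90%, equal allocation.

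n per arm = 2 × SD² × (1.960 + 1.282)² / (margin − difference)²

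- With −1.01 h: 2 × 25 × 10.51 / 1.76² = 169.6, so 170, against the stated 164. Power at 164 per arm is 0.890.
- With 70% of the stated 1.5 h, that is −1.05 h: 2 × 25 × 10.51 / 1.80² = 162.2, so 163 (164 with the t distribution), which matches the plan. Power at 164 per arm is 0.903.

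The point made here does not depend on which difference was used.

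**Loss of precision if consent withdrawals are dropped**

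The protocol gives no withdrawal rate. Its 5% dropout figure refers to patients ventilated for less than 2 h. The rates below are assumptions.

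Power = Φ[(0.75 − difference) / (5.0 × √(2/n)) − 1.960], with n = 328 × (1 − rate) / 2

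| Share of 328 excluded | Patients | Power at −1.01 h | Power at −1.05 h |
|---|---|---|---|
| 0% | 0 | 0.890 | 0.903 |
| 1% | 3 | 0.887 | 0.900 |
| 2% | 7 | 0.884 | 0.897 |
| 5% | 16 | 0.874 | 0.888 |
| 10% | 33 | 0.856 | 0.871 |

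**Possible shift in one arm's mean duration**

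If a share w of an arm is dropped and those patients average d hours above the patients who remain, the arm mean moves by w × d. Both w and d are assumptions.

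| w in one arm | d = 1 h | d = 3 h | d = 3 h, as share of 0.75 h |
|---|---|---|---|
| 1% | 0.01 h | 0.03 h | 4% |
| 2% | 0.02 h | 0.06 h | 8% |
| 5% | 0.05 h | 0.15 h | 20% |
| 10% | 0.10 h | 0.30 h | 40% |

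In whole patients, the 5% row is 8 × 3 h / 164 = 0.146 h. The difference between arms moves by the w × d of one arm minus that of the other, so similar withdrawal in both arms largely cancels.

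**The case against.** The best counter-argument rests on a qualifier. Statistical analysis excludes patients lost to follow-up because consent was withdrawn, not everyone who withdrew. A patient whose 2 h window and extubation are on file is arguably not lost for those outcomes, and on that reading the two sections fit together. The reading is possible, but the protocol does not state it. It would also leave the exclusion with nothing to do, because the complete-case rule already removes patients from any outcome that they lack. Redundancy is not proof of contradiction, so the fair statement is a conflict on the plain reading, with an unstated alternative.

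A reader might go further in three ways that the document does not support.

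- **That all withdrawn patients are affected.** Statistical analysis names only withdrawal of consent and cancelled surgery. Patients withdrawn by the investigator for medical reasons, plausibly the group most closely linked to how ventilation went, fall under one rule only, and their data are used.
- **That excluding cancelled surgeries biases the ventilation outcomes.** Such patients have no postoperative ventilation to measure, and randomisation waits until surgery is certain to proceed.
- **That the set can be picked once results are known.** Analyses are to be fixed before the database closes, the analyst is blinded to allocation, and a full analysis plan is to be published beforehand. These safeguards limit that risk considerably. They do not reconcile the two sentences, which the author of that plan would inherit.

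**Conclusion.** The point stands for withdrawal of consent after randomisation. Two current sentences give different answers about whether recorded outcomes are analysed, and the plain reading of one creates a post-randomisation exclusion that is not needed.

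The expected size is small. Statistical analysis anticipates no or minimal losses. At 1% to 2% excluded, power for the non-inferiority endpoint falls by less than one percentage point. It would be tempting to present 0.15 h, a fifth of the margin, as the likely bias. The document does not support that: it gives neither a withdrawal rate nor durations for patients who withdraw, and the figure assumes 5% withdrawal in one arm, all well above the mean, with nothing offsetting it in the other. The case for change rests on fixing who is analysed, not on a demonstrated bias or loss of power.

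The separate exclusion of patients ventilated for less than 2 h from the quality and workload endpoints is not part of this point.

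**What to change.** Keep the rule in Study dropouts and missing data, and amend Statistical analysis to match. Suggested wording: *Patients are analysed in the arm to which they were randomised. All outcome data captured before withdrawal of consent are included, unless the patient refuses use of the data. A patient is excluded only from outcomes that were not captured. Consent withdrawals, refusals of data use and cancelled surgeries are reported by arm.*

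The refusal clause is not in the current text and is itself a post-randomisation exclusion, which is why refusals should be counted by arm. Use the same analysis-set label in Statistical analysis and in the Discussion.

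The cost is a few lines in the protocol or in the promised final analysis plan. No new data are needed, since the protocol already has data up to withdrawal stored.

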### Handling of data

All of the patients directly identifying personal data (e.g., name, address, email, etc.) will be separated from the research data (e.g., measurement data, etc.) and replaced by an assigned code. The directly identifying data will be only used to contact the patients and only available to the local investigators. The handling of personal data complies with the general data protection regulations (GDPR) and applicable national regulations. To perform data collection and validation, an electronic case report form (eCRF), including validation checks and appropriate user access rights, will be set up in Castor EDC (www.castoredc.com). This application is a GCP compliant application that meets the standard for information security management. All data will be stored in a secure place for 15 years after termination of the study. Electronic files will be archived on a trial-designated folder on the cloud server of the respective participating center in a secure and controlled environment to maintain confidentiality. Electronic files will be controlled with password protection according to best practices. A GCP-certified monitor will monitor the study according to ICH–GCP guidelines throughout its duration. Any data leaks that might occur regardless of these safety precautions will be reported to all parties within one working day after discovery of the leak.

The objective of the clinical data management plan is to provide high-quality data by adopting standardized procedures to minimize the number of errors and missing data and, consequently, to generate an accurate database for analysis.

Accuracy and consistency checks will be carried out by way of automatic validation, pre-specified, and ad hoc checking by personnel at the coordinating centers. A qualified monitor will be installed to perform study monitoring according to the monitoring plan. Remote monitoring will be performed to signal early aberrant patterns, issues with consistency, credibility, and other anomalies. Onsite monitoring will comprise controlling presence and completeness of the research dossier and the informed consent forms, and source data checks will be performed as described in the monitoring plan.

Amendments are changes made to the research after a favorable opinion by the accredited Institutional Review Board (IRB) has been given. All amendments will be notified to the IRB that gave a favorable opinion. Non-substantial amendments will not be notified to the accredited IRB and the competent authority but will be recorded and filed by the sponsor. A “substantial amendment” is defined as an amendment to the terms of the METC application, or to the protocol or any other supporting documentation, that is likely to affect to a significant degree: the scientific value of the trial or the quality or safety of any intervention used in the trial. Any proposed amendments will first be notified to the sponsor. Following approval from the sponsor, the principal investigator (PI) will notify all participating centers of the changes. This ensures consistent implementation of the updated protocol across all trial sites. Any deviations from the protocol will be fully documented using a breach report form. This documentation will include the nature of the deviation, the reason for it, and any corrective actions taken. The protocol will be updated in the clinical trial registry to reflect any major changes.

### Sample size calculation

For the analysis of quality of ventilation, we need at least 110 patients in each arm of the study. We expect a dropout rate of 5%, as some patients may be liberated from the ventilator earlier. To correct for these dropouts, we propose to continue recruiting and randomizing patients until we have a sufficiently large sample size, i.e., we continue the study until we have 220 patients that have received postoperative ventilation for at least 2 h.

In regard of the secondary outcome, to demonstrate if automated ventilation by means of INTELLiVENT-ASV is non-inferior to non-automated ventilation by means of conventional ventilation with respect to duration of postoperative ventilation, we expect to need more patients for the analysis of this endpoint then for the other (primary) endpoints. Based on two recent randomized clinical trials in comparable patient groups, i.e., “POSITiVE” [17] and one comparing INTELLiVENT-ASV using mainstream end-tidal CO_2_ (etCO_2_) monitoring with INTELLiVENT-ASV using sidestream etCO_2_ monitoring (named “INTELLiSTREAM”) [18], we conservatively estimate to need 164 patients in each arm of the study (i.e., a total number of 328 patients is needed). The standard deviation for the duration of postoperative ventilation was found to be 3.9 h in POSITiVE [17] and 2.7 h in INTELLiSTREAM [18]. Based on these data, the true mean difference between INTELLiVENT-ASV and conventional ventilation in duration of postoperative ventilation is 1.5 h. Considering a standard deviation of 5.0 h (to account for imprecision), a true mean difference of − 1.01 (conservative estimate from POSITiVE, 70% of the effect in the study), an alpha of 0.025, a power of 90%, and equal allocation between the groups, therefore 164 patients in each arm is needed considering a margin of non-inferiority of ¾ h. Finally, a total of 328 patients will be included to the study.

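### Sample size: the printed inputs for non-inferiority on duration of ventilation give 170 or 171 patients per arm, not 164 (minor, about one point of power)

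*Protocol article*

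**What the plan says.** All the ingredients are in the Sample size calculation section of the protocol article.

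- The primary endpoint needs at least 110 patients per arm. Duration of ventilation is treated separately, because "we expect to need more patients for the analysis of this endpoint then for the other (primary) endpoints".
- The SDs in the two source trials were 3.9 h and 2.7 h. The plan uses a larger one: "Considering a standard deviation of 5.0 h (to account for imprecision").
- The difference between the ventilation strategies is given as 1.5 h. The calculation then uses -1.01 h, described as a "conservative estimate from POSITiVE, 70% of the effect in the study".
- The margin is three quarters of an hour. The rest of the statement reads "an alpha of 0.025, a power of 90%, and equal allocation between the groups, therefore 164 patients in each arm is needed", and the total is 328.
- The Statistical analysis section confirms that the 0.025 is one-sided: "a one-sided noninferiority hypothesis test with a significance level of 0.025".

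Two further sentences bear on how 328 is read. The section on dropouts and missing data says "A dropout rate of 5% has been accounted for in the sample size". The primary-endpoint paragraph of the Sample size calculation section says "we continue the study until we have 220 patients that have received postoperative ventilation for at least 2 h".

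**The concern.** The section prints every input and the result, so a reader can redo the sum, and it does not come out. There are two mismatches, and they point the same way. The difference of -1.01 h is too small to give 164 per arm. It is also not 70% of the 1.5 h given in the same paragraph. At least one of the four figures (1.5 h, 70%, -1.01 h, 164) is therefore misprinted, rounded differently from the others, or taken from another calculation.

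This calculation fixes the size of the whole trial. If -1.01 h is the real assumption, the stated 90% power is not what 164 per arm delivers. If -1.05 h was used, the size is sound and the published assumption is wrong.

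**Working it through.** **Inputs.** SD 5.0 h, margin 0.75 h, true difference -1.01 h, 90% power and equal arms come from the Sample size calculation section. One-sided alpha 0.025 comes from there and from the Statistical analysis section.

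**Formula.** For non-inferiority of two means, n per arm = 2 × [SD × (z(0.975) + z(0.90)) / (margin − difference)]², with z(0.975) = 1.960 and z(0.90) = 1.2816. The numerator is 5.0 × 3.2416 = 16.208.

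**Step 1: the printed inputs.** Margin − difference = 0.75 + 1.01 = 1.76 h. Then n = 2 × (16.208 / 1.76)² = 169.6, so 170 per arm. The exact noncentral t calculation gives 171. The plan prints 164, which is 6 to 7 patients per arm fewer (3.7% to 4.3% of 164).

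**Step 2: the described effect.** 0.70 × 1.5 h = 1.05 h. Margin − difference = 0.75 + 1.05 = 1.80 h. Then n = 2 × (16.208 / 1.80)² = 162.2, so 163 per arm. The noncentral t gives 164, which is the plan's figure.

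**Step 3: other ways to reach 164 from -1.01 h.** One input is changed at a time.

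| Change | n per arm (z / t) |
|---|---|
| One-sided alpha 0.05 | 139 / 139 |
| One-sided alpha 0.0125 | 201 / 202 |
| Power 80% | 127 / 128 |
| Power 85% | 145 / 146 |
| Power 89% | 164 / 165 |
| SD 3.9 h | 104 (z) |

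Only a power of 89%, which the plan does not state, gives 164 with -1.01 h.

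**Step 4: power at 164 per arm with -1.01 h.** The standard error is 5.0 × √(2/164) = 0.552 h. Then 1.76 / 0.552 − 1.960 = 1.23, which gives a power of 89.0% (z). The noncentral t gives 88.8%. With -1.05 h the noncentral t gives 90.2%.

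**Step 5: can rounding explain it?** A value printed as 1.01 lies between 1.005 and 1.015. Dividing by 0.70 gives 1.436 to 1.450. A value printed as 1.5 lies between 1.45 and 1.55. The two ranges just touch at 1.45 h, where 70% is 1.015 h. Margin − difference is then 1.765 h, and n = 2 × (16.208 / 1.765)² = 168.7, so 169 per arm (z). Rounding could at most reconcile 1.5 h with -1.01 h; it does not recover 164. Under the z formula, 164 corresponds to a difference of about -1.04 h.

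**Step 6: the total.** 2 × 164 = 328, so nothing has been added for loss on the duration endpoint.

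**The case against.** The best defence is that the error changes nothing in practice. It is worth about one point of power on a secondary endpoint. The SD of 5.0 h was set above both source trials on purpose. At an SD of 3.9 h and -1.01 h, 164 per arm would give 98.3% power (1.76 / (3.9 × √(2/164)) − 1.960 = 2.13). The primary endpoint needs 220 evaluable patients and 328 are planned. It is also only an inference that -1.05 h was used: it matches 164 exactly only under the t method, which the article does not name. All of this stands, and it limits the weight of the point. It does not make the printed figures agree.

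Two stronger readings are tempting, and the article does not support them.

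- **That 5% of patients will be lost on duration, so 328 is clearly too few.** The 5% concerns patients ventilated for less than 2 h, who count as dropouts for quality of ventilation and workload only. A patient extubated early still has a duration of ventilation. The article expects no or minimal losses on the secondary outcomes. Some loss is possible: randomisation precedes surgery, some exclusions apply at its end, withdrawals after randomisation are not replaced, and withdrawn consent or cancelled surgery leaves the analysis. No rate is given for this, so any power or size based on 5% loss would be the reader's own assumption.
- **That recruitment could stop at 220 evaluable patients and leave the non-inferiority test badly underpowered.** The section moves from the primary endpoint to the larger need for duration and ends with 328 in total. The abstract also says that 328 will be randomised. Read whole, 220 is the evaluable minimum for the primary endpoint. The wording is loose, but it is not a competing stopping rule.

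**Conclusion.** Wrong as written, and minor. The printed inputs require 170 (z) or 171 (t) patients per arm, not 164. With -1.01 h, 164 per arm has 88.8% (t) to 89.0% (z) power against the stated 90%. The -1.01 h also does not match 70% of the printed 1.5 h, whereas 1.05 h does, and it gives 163 (z) or 164 (t). A misprinted or differently rounded difference is the likelier cause, but the article does not settle it.

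The result assumes a comparison of two means with a common SD of 5.0 h, equal arms and one-sided 0.025, all as the plan states. It does not affect the primary endpoint, and it does not show that the trial is too small.

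**What to change.** Reconcile the four figures (1.5 h, 70%, -1.01 h and 164) against the original calculation, in one of two ways:

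- if -1.05 h was used, print -1.05 h and name the t-based method, which keeps 164 per arm and 90% power; or
- if -1.01 h was used, keep it, correct the 1.5 h or the 70% so that they agree with it, and restate the power at 164 per arm as about 89%.

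As a wording clarification only, say that 220 patients ventilated for at least 2 h is the evaluable minimum for the primary endpoint, that recruitment ends at 328 randomised, and that 328 is 2 × 164 with no allowance for loss after randomisation on duration.

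The cost is a few words in the protocol and, under the second option, a stated power one point lower. No extra patients and no change to the analysis are needed.
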